### Criteria for discontinuing or modifying allocated interventions {11b}

Participants are free to withdraw their consent to participate at any time for any reason if they wish to do so, without any consequences or need for an explanation. The investigator holds the prerogative to terminate a participant’s participation in the study in instances of non-compliance, such as medication adherence. In situations where participants encounter side effects resulting in substantial harm or rendering continued participation unfeasible, the investigator may opt to remove the participant from the study, particularly in the event of a serious adverse event [25].

### Strategies to improve adherence to interventions {11c}

A systematic review of medication non-adherence in individuals with cognitive impairment underscores the susceptibility of elderly individuals diagnosed with MCI and mild dementia to non-adherence, given the cognitive demands inherent in medication management [26]. Accordingly, we will incorporate a study medication diary as an intervention to enhance medication adherence. The diary will inform them about optimal storage and administration practices for the study medication, along with guidance for instances where participants have forgotten to take a capsule. Participants will be required to record daily whether they have adhered to the medication schedule and at what specific time. Additional space has been added for participants to document any particularities, comments, side effects, or other noteworthy observations. Note that the study medication diary answers are not an outcome of the study and thus will not be analyzed. To further increase medication adherence, participants will receive a pill box to facilitate the organized distribution of capsules throughout the week. The provision of additional capsules will serve as a contingency for unforeseen accidents, such as dropping a capsule in the sink, while also serving as a metric for evaluating medication adherence. Unused capsules and bottles will be collected during the 12-week and 24-week visits, with the trial pharmacy documenting and quantifying any surplus study medication. An effort will be made by the researcher to involve a committed (informal) caregiver of the participant to monitor medication adherence. Additionally, regular bi-weekly calls from the research team will provide a platform for participants to discuss and address any challenges or concerns related to the study medication and medication adherence.

### Relevant concomitant care permitted or prohibited during the trial {11d}

All concomitant care, except treatment with opiates and benzodiazepines, is permitted during the trial. Treatment with opiates and benzodiazepines is known to affect memory, and thus anyone using opiates and/or benzodiazepines will be excluded from the study. Comprehensive documentation of all other concomitant care will be recorded in the electronic case report form (eCRF). Participants are expected to adhere to their regular medication regimens for the management of pre-existing conditions throughout the trial period.

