Our secondary objectives encompass a comprehensive exploration of diverse cognitive domains. Included cognitive domains are as follows: mental speed/attention and executive functioning (Letter Digit Substitution Test (LDST) and Trail Making Test (TMT)), spatial memory (Spatial Pattern Separation Task), language (Alzheimer’s Disease Assessment Scale-Cognitive Subscale (ADAS-Cog), and the Shortened Boston Naming Test-15 (BNT-15)) and orientation (Mini-Mental State Examination (MMSE)) will be measured as well. In addition to cognitive assessments, we aim to gauge participants’ quality of life (Quality of Life AD (QoL-AD), EuroQol-5 Dimensions (EQ-5D)), psychological well-being (Hospital Anxiety Depression Scale; HADS), neuropsychiatric symptoms (Neuropsychiatric Inventory; NPI), and daily functioning (Alzheimer’s Disease Cooperative Activities of Daily Living Scale; ADCS-ADL). This multifaceted approach aims to illuminate the intricate interplay between cognition, quality of life, mood, and emotion. Outcome measures include a decrease in the reaction time (RT) in the LDST and TMT, as well as a decrease in errors in the LDST. Anticipated improvements encompass an increased total recognition score on the 15-VLT and an increased accuracy in all identified pattern completion scores of the pattern separation memory task. Total scores on the MMSE and ADAS-cog are expected to improve, as well as increased scores in well-being and quality of life, as indicated by the participant and the (informal) caregiver questionnaires. Furthermore, tau measurements from tear fluid samples will be assessed, as we speculate a potential positive impact of roflumilast on phosphorylated tau (pTau) concentrations [22]. Lastly, we will monitor the conversion from (a)MCI to dementia.

Three primary hypotheses have been formulated:The administration of 50 μg roflumilast over a chronic treatment period of 24 weeks, compared to placebo, is anticipated to improve episodic memory in participants with aMCI or mild AD dementia;The administration of 100 μg roflumilast over a chronic treatment period of 24 weeks, compared to placebo, is anticipated to improve episodic memory in participants with aMCI or mild AD dementia;The administration of 50 μg roflumilast over a chronic treatment period of 24 weeks, compared to 100 μg roflumilast, is anticipated to have comparable effects on episodic memory in participants with aMCI or mild AD dementia.

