Individuals undergoing current irradiation are excluded from the study as irradiation can cause radiation-induced cognitive impairment. Individuals who have a Fazekas score of 3 and higher on MRI scans are excluded as it indicates a mixed (AD and vascular) or vascular origin of cognitive impairment. Individuals with chronic viral infections (human immunodeficiency virus, and hepatitis B and C) are excluded from the study due to the possible risk of treatment-related toxicity. Normal pressure hydrocephalus (NPH), Morbus Huntington, Parkinson’s disease, recent transient ischemic attack (TIA), or cerebrovascular accident (CVA) within the last 2 years, TIA/CVA followed by a cognitive decline within 3 months are all exclusion criteria because of the cognitive impairment related to these disorders. COPD (gold criteria 3 and 4) are exclusion criteria due to the medication used in this study trial and its original indication. Roflumilast is a possible add-on treatment for COPD and severe asthma. Accordingly, although the dosage in this study is substantially lower than usually is prescribed in COPD patients (250 or 500 μg), we want to avoid cognitive improvement due to the improvement of any COPD-related symptoms. A lifetime history of schizophrenia, bipolar disorder, or psychotic symptoms not otherwise specified, current affective disorder (anxiety or major depression), cognitive problems due to alcohol abuse, brain tumours, epilepsy, and encephalitis are exclusion criteria because of the possible (temporary) cognitive impairment associated with these disorders. Other exclusion criteria are current treatment with (or other use of) cannabis, opiates, benzodiazepines, methylenedioxymethamphetamine, and cocaine. The use of medications strongly inhibiting CYP3A4 or CYP1A2 is also an exclusion criterion because of the interference with roflumilast metabolism resulting in the reduced therapeutic effectiveness of roflumilast. Individuals with rare hereditary problems of galactose intolerance, Lapp lactase deficiency, or glucose-galactose malabsorption will be excluded, as both the placebo and roflumilast contain lactose monohydrate. Moreover, participants are not allowed to participate in other drug trials during the study period. Lastly, participants unable to be accompanied at every test session by the same (informal) caregiver will be excluded. Roflumilast is contraindicated in individuals with moderate to severe liver impairment (e.g. Child–Pugh B and C) and those with hypersensitivity to the active substance or any of the listed excipients, namely, lactose monohydrate, corn starch, povidone, and magnesium stearate, will also be excluded from the study.

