#### Other outcomes

We aim to conduct a pharmacokinetic validation of roflumilast and its active metabolite roflumilast N-Oxide in blood plasma at T1 (acute test day), T2 (3-month test day), and T3 (6-month test day). As this is the first study to investigate a dose of 50 μg of roflumilast, a previous pharmacokinetic validation has never been performed for this dose specifically. Considering the inverted U-shaped dose–response curve, we expect 50 μg to reach the same effectiveness as 100 μg by likely achieving similar plasma levels after chronic administration. The outcome should determine approximately the same plasma level of roflumilast and its active metabolite per participant at measurements T2 (3 months) and T3 (6 months) if the participant complied with study medication adherence. We expect participants who were allocated in the 50 μg condition to have lower plasma levels than participants who were allocated in the 100 μg condition at the acute measurement. At the beginning of participation, participants will be required to complete a concise questionnaire, capturing essential demographic and lifestyle variables. This includes the date of birth, age, sex, highest education completed, civic status, living situation, housing situation, ethnicity, height, weight, amount of smoking per day, average alcohol intake per week, relationship with the (informal) caregiver, and any positive family history pertaining dementia, Parkinson’s disease, or amyotrophic lateral sclerosis. Upon study completion, a follow-up assessment will be conducted to identify any changes in the aforementioned variables. In addition to these demographic aspects, tau in tear fluid will be measured. Based on the current literature, it is possible to measure tau in tear fluid [22]. Our study aims to discern whether roflumilast induces changes in tau concentrations within tear fluid. The statistical analysis will focus on changes from baseline to the 6-month mark. Furthermore, vigilant monitoring of adverse events (AEs) and serious adverse events [25] will be integral to our study.

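### The on-trial rule in {11d} permits strong CYP3A4/CYP1A2 inhibitors and cannabis treatment that bar entry under {10}; the main cost is to the T2–T3 plasma check

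*Protocol article*

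**What the plan says.** Eligibility criteria {10} exclude interacting drugs: "The use of medications strongly inhibiting CYP3A4 or CYP1A2 is also an exclusion criterion because of the interference with roflumilast metabolism", with the stated consequence "resulting in the reduced therapeutic effectiveness of roflumilast". The same section excludes "current treatment with (or other use of) cannabis, opiates, benzodiazepines, methylenedioxymethamphetamine, and cocaine".

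For the treatment period, {11d} states: "All concomitant care, except treatment with opiates and benzodiazepines, is permitted during the trial". It explains the two exceptions by their effect on memory, sends all other care to the eCRF, and adds: "Participants are expected to adhere to their regular medication regimens for the management of pre-existing conditions throughout the trial period".

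Under Other outcomes, roflumilast and its N-oxide are measured at T1, T2 and T3. The expectation is "approximately the same plasma level of roflumilast and its active metabolite per participant at measurements T2 (3 months) and T3 (6 months"), on one condition: "if the participant complied with study medication adherence".

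**The concern.** The reason given for excluding inhibitors concerns how roflumilast is metabolised. It cannot matter before the first capsule and matters throughout treatment. Yet the section that governs treatment is worded as a complete rule with two exceptions, and inhibitors are not among them. Someone who could not enter on such a drug may start it the day after randomisation. Cannabis treatment stands in the same exclusion list as opiates and benzodiazepines and is released in the same way. The sentence on regular regimens concerns drugs already taken for existing conditions and does not stop a new prescription.

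The plasma check is what is mainly at stake. It reads a stable level from T2 to T3 as a sign of adherence and makes no allowance for a change in metabolism. Plasma levels also serve as the first pharmacokinetic validation of 50 µg, in an arm of only 27.

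**Working it through.** **1. The rules side by side**

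| Treatment | At entry, {10} | During treatment, {11d} |
|---|---|---|
| Opiates, benzodiazepines | barred | barred |
| Cannabis treatment | barred | permitted |
| Strong CYP3A4/CYP1A2 inhibitors | barred | permitted |

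No other section restricts inhibitors after entry. Section {11b} covers withdrawal, non-compliance and side effects, not a newly started drug.

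**2. The plasma check**

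Suppose an inhibitor multiplies the steady level by a factor k in a participant who takes every capsule. If it is in use at T3 but not at T2, the ratio T3/T2 is k. If it is in use at T2 but not at T3, the ratio is 1/k. The check expects about 1, so any k clearly different from 1 breaks it with no capsule missed. The document gives no value of k and no direction for the change in level.

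For scale, {11a} gives a half-life of 30 h for the N-oxide. With first-order elimination (assumed), one capsule missed just before sampling leaves 2^(−24/30) = 0.574 of the usual level, a fall of 43%. An interaction that multiplied the level by 0.574, or the end of one that had raised it 1/0.574 = 1.74-fold, would look like one recently missed capsule. Whether a real interaction would be that large is not known from the document.

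The same half-life gives a minimum wait before a sample is usable again: 5 × 30 h = 150 h = 6.25 days, rounded up to 7. A long-acting inhibitor would need longer.

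**3. The primary contrast**

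Inputs from the document: 24 per group, raised for dropout to 24/(1 − 0.10) = 26.7, so 27; two roflumilast arms, 2 × 27 = 54 participants; d = 0.69 from {14}.

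Assumptions, none from the document: a share p of 1–5% start such a drug and use it at the 24-week test, and each loses a fraction L of 25–100% of the effect, in the direction {10} states.

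- Expected starters: 54 × 0.01 = 0.54 to 54 × 0.05 = 2.7.
- Chance of at least one: 1 − 0.99^54 = 0.42 to 1 − 0.95^54 = 0.94.
- Dilution 0.69 × p × L: 0.69 × 0.01 × 0.25 = 0.0017 SD to 0.69 × 0.05 × 1 = 0.0345 SD, which is 0.25% to 5% of d.
- Power of a one-way F-test (f = d/2 = 0.345, 24 per group) with full loss of effect: 0.729 without starters, 0.720 at 1% and 0.682 at 5%, a loss of about 1 to 5 points. Section {14} does not say which F-test was planned, so only these differences are used.

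**The case against.** Section {10} governs entry and {11d} governs later care, so they are not opposite statements about the same moment. The sentence in {11d} on opiates and benzodiazepines reads like a short restatement of eligibility, and a condensed article may leave a list of interacting drugs to the full protocol. This justifies calling the matter an inconsistency and no more. It does not remove it, because the article states a categorical permission that is too broad, rather than leaving a detail out.

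Safeguards also exist and stand. Concomitant care is recorded in the eCRF, the trial pharmacy counts unused capsules at 12 and 24 weeks, and no stated rule classes anyone as non-adherent on plasma level alone. Affected samples could therefore be found later, though without a rule set in advance the choice would be made after seeing the data.

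A reader might infer more than the document supports:

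- *That a changed level equals many missed capsules over 12 weeks.* It does not. One sample reflects the last few days, and a single missed capsule already lowers the N-oxide level by about 43%.
- *That inhibitors blur an exposure gap on which the third hypothesis rests.* That hypothesis says 50 µg compared with 100 µg "is anticipated to have comparable effects on episodic memory in participants with aMCI or mild AD dementia". Other outcomes ties it to similar plasma levels after chronic dosing and expects lower levels at 50 µg only at the acute measurement. The hypothesis does not rely on a gap at T2 or T3.
- *That inhibition is known to weaken the effect.* Section {10} asserts this, but the document does not show it. If exposure rose instead, {6b} reports nausea and diarrhoea above 100 µg without a proportional cognitive gain, so avoiding the interaction makes sense either way.
- *That the fix restores the planned effect size.* It would not, because medically needed courses are still given and their 15-VLT scores still analysed.

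**Conclusion.** The inconsistency is real and minor. Strong CYP3A4/CYP1A2 inhibitors and cannabis treatment bar entry but may be started once treatment begins, and the stated reason for excluding inhibitors applies only during treatment. For inhibitors, the consequence that follows from the text is that the T2–T3 plasma level can shift in an adherent participant; its size and direction are unknown. The effect on the primary contrast is at most about 0.035 SD under the assumed 1–5% of starters and 25–100% loss of effect, which would not change a conclusion. The amendment is worth making because it costs almost nothing, not because the main result is at risk.

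**What to change.** Reword the opening of {11d}: *All concomitant care is permitted during the trial except opiates, benzodiazepines, cannabis and drugs strongly inhibiting CYP3A4 or CYP1A2, for which an alternative is used where one exists.*

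Then add: *If such a drug is medically needed, it is given, its dates are recorded in the eCRF, and the participant stays in the study with all visits and all 15-VLT scores analysed. Plasma samples taken during the course of an inhibitor, or for at least 7 days after it, are left out of the T2–T3 adherence comparison.*

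The cost is a short amendment, one question in the existing bi-weekly calls, and slightly fewer plasma samples in the adherence comparison. Eligibility, visits, sample size and the primary model do not change.

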### Provisions for post-trial care {30}

Participants are informed in the participant information sheet that insurance is provided for everyone participating in this study. The insurance covers damages/harm caused by the study; however, not all damages/harm are covered. In the participation information sheet, we inform participants that insurance does not apply if the risk occurs more seriously than was foreseen or if the risk is very unlikely; harm to his/her health that would also have occurred if they had not participated in this study; harm to their result, as a result of a negative effect of the study on them or their children and damage due to an existing treatment method in the case of existing treatment methods. The insurance provides coverage of at least 650,000 euros per participant and at least 5,000,000 euros for the entire study. The insurance applies to harm during the study or within 4 years of the end of the participation in the study. These provisions can be found in the “Decree on Compulsory Insurance in Medical Scientific Research with Humans 2015.” This decree can be found in the Government Law Database (https://wetten.overheid.nl). Participants are informed in the participant information sheet that the study medication is not distributed post-trial participation.

### Outcomes {12}

#### Primary study parameter

The primary outcome measure is verbal memory using the 15-VLT [27]. The 15-VLT is chosen as our primary outcome because it assesses episodic memory—a cognitive domain linked with hippocampal function [18]. Considering the evidence of high PDE4 expression in the hippocampus [19] and observable atrophy in the medial temporal lobe regions of individuals diagnosed with MCI [17, 20]. Accordingly, a larger effect size for cognitive functions and tasks related to this brain area is expected. Variables include correct immediate recall on trial 1 to trial 5, correct total immediate recall (sum of all 5 trials), and correct delayed recall. Change from baseline to acute effects, change from baseline to 3 months, change from baseline to 6 months, and 6 months to follow-up will be statistically analysed.

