### Objectives {7}

This study aims to examine whether a 24-week administration of roflumilast improves cognition in participants with (a)MCI and/or participants with mild AD dementia. The outcomes may provide a proof of concept on the potential of roflumilast as a pharmacotherapeutic treatment to enhance cognition, concurrently advancing our comprehension of the role played by PDE4 in human cognition. The primary objective is to validate the effect of roflumilast on episodic memory, assessed with the 15-word verbal learning test (15-VLT), in aMCI/mild AD dementia participants after chronic roflumilast treatment of 24 weeks (i.e. 6 months). Specifically, we expect an increase in correct recall of words on the immediate and delayed recall. The 15-VLT is particularly relevant, as it assesses episodic memory, a function primarily associated with the hippocampus [18]. Considering the evidence of high PDE4 expression in this specific brain structure [19] and observed (early) atrophy of the medial temporal lobe regions in (a)MCI/mild AD [17, 20], we expect a larger effect size for cognitive functions and tasks related to this brain area. Moreover, Hamel and colleagues have demonstrated the prognostic value of the 15-VLT performance decline, predicting dementia approximately 7 years preceding the formal diagnosis [21]. This temporal insight underscores the test’s relevance and its potential to serve as a sensitive indicator of cognitive trajectories in the context of (a)MCI and mild AD.

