### Statistical methods

#### Statistical methods for primary and secondary outcomes {20a}

Descriptive statistics for continuous parameters will include sample sizes, means and standard errors of the dependent variables, and covariates for each distinct level combination of factors. For categorical data, summary tables will present counts and percentages. Statistical summaries will be presented by treatment, sequence, or period. The repeated measures, namely the outcome variables of the cognitive assessments and the subjective well-being-related scales, will be analysed using mixed models. The between-subject factor will be the treatment group (three levels: placebo, 50 μg roflumilast, and 100 μg roflumilast). The scores of each task will be entered as the within-subject factor, as well as time (T1, i.e. acute, T2, i.e. 12 weeks, T3, i.e. 24 weeks, T4, i.e. 2-week follow-up). An additional interaction term between the treatment group and time is included to determine whether the different treatment groups will lead to different trajectories over time. Subject covariates included will be sex, age, and education. Additionally, at the end of the study, we will ask each participant which intervention arm they think they have received (placebo, 50 mcg roflumilast, or 100 mcg roflumilast). Because of exclusion and inclusion criteria related to the patient recruitment of the study, the population recruited will be homogenous. Note that groups will not be able to be matched because of the applied randomization block strategy. The significance level will be set at *a* = 0.05.

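### The primary endpoint is defined inconsistently: section {12} gives equal primary status to seven 15-VLT variables and four change windows, while the objectives point to immediate and delayed recall at 24 weeks, and only a single 0.05 level is stated

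*Protocol article*

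**What the plan says.** Outcomes {12}, Primary study parameter, names the 15-VLT as the primary outcome and continues: "Variables include correct immediate recall on trial 1 to trial 5, correct total immediate recall (sum of all 5 trials), and correct delayed recall". The windows to be analysed are "Change from baseline to acute effects, change from baseline to 3 months, change from baseline to 6 months, and 6 months to follow-up". The follow-up visit is at week 26, two weeks after the 24-week treatment period. The section puts no variable or window ahead of another. The section on secondary parameters applies the same four windows to every secondary outcome.

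Other sections of the protocol article are narrower:

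- Objectives {7} places the primary objective "in aMCI/mild AD dementia participants after chronic roflumilast treatment of 24 weeks (i.e. 6 months") and adds that "we expect an increase in correct recall of words on the immediate and delayed recall". It also says "Three primary hypotheses have been formulated". Two of these set a dose against placebo, the third expects the two doses to be comparable, and all three concern 24 weeks of treatment.
- The 15-VLT description under {18a} gives total immediate recall and delayed recall as key measures. Recognition also appears there, but {12} makes it secondary. Single-trial scores are not among them.
- Participant retention {18b} counts a participant as a dropout if the 15-VLT is missing at baseline or at 6 months. The other visits do not count.
- Sample size {14} uses one effect size, 0.69, without naming the variable.

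On testing, Statistical methods {20a} plans mixed models, says "An additional interaction term between the treatment group and time is included", and closes with "The significance level will be set at *a* = 0.05". It designates no contrast as primary and gives no ordering.

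**The concern.** A trial needs one statement of what counts as success. Here the section that should give it is broader than the objective, the hypotheses and the missing-data rule. Five of its seven variables are components of a sixth. Two of its four windows, the acute change and the change after dosing ends, do not address a 24-week treatment effect.

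Without a designated variable and time point, a reader of the results cannot tell which of several recall findings the trial was designed to test, and part of that choice could be made after the data are seen. The article says a positive outcome may lead to a phase III trial. It also plans an unblinded interim analysis, after half the participants have finished, that will inform a patent decision.

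**Working it through.** The article gives no family-wise error figure to reproduce. Its one related calculation, the dropout allowance, reproduces: 24 / (1 − 0.10) = 26.7, rounded up to 27 per arm.

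**Inputs from the article.** Seven variables and four windows ({12}), two doses against placebo ({7}), a level of 0.05 ({20a}) and 24 per arm after dropout ({14}).

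**Assumptions.** Tests are two-sided, since sidedness is not stated. Correlations are not given, so a range is used: 0.3 to 0.95 between variables at a visit, and 0.3 to 0.9 between visits.

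**Count on the broadest reading.** 7 × 4 × 2 = 56 contrasts against placebo.

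**Bound if tests were independent.** 1 − 0.95^k:
- k = 2: 9.75%
- k = 4: 18.5%
- k = 7: 30%
- k = 14: 51%
- k = 56: 94.3%

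**Simulation with correlation.** No drug effect, 24 per arm, five visits, five trial scores plus their sum plus delayed recall. Each dose is compared with placebo on change scores by t-test at two-sided 0.05. The omnibus row is the treatment-by-time F test for each variable. There were at least 5,000 simulated trials per setting. The table gives the chance of at least one rejection at a between-visit correlation of 0.6.

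| Reading | Tests | 0.3 | 0.5 | 0.7 | 0.9 | 0.95 |
|---|---|---|---|---|---|---|
| One variable, 24 weeks, two doses | 2 | 9% | 9% | 9% | 9% | 9% |
| Total and delayed recall, 24 weeks, two doses | 4 | 16% | 15% | 14% | 12% | 11% |
| Omnibus treatment-by-time test per variable | 7 | 26% | 21% | 18% | 11% | 9% |
| All seven variables, 24 weeks, two doses | 14 | 40% | 35% | 28% | 20% | 16% |
| All variables, windows and doses | 56 | 83% | 78% | 68% | 53% | 44% |

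Columns are the between-variable correlation. Other between-visit correlations and repeat runs move entries by a point or two, so the ranges quoted elsewhere are slightly wider: 11–17%, 16–42% and 44–84%. For the omnibus tests the range is 9–26% under correlation and 30% if independent.

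**Benefit direction only.** Over all 56 contrasts, a false finding of benefit occurs in about 56% of trials at a between-variable correlation of 0.3 and 30% at 0.9. For one variable and two doses the independent bound is 1 − 0.975² = 4.9%, against 2.5% for a single comparison.

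**Power cost of controlling two doses.** Per-arm size for a plain two-group comparison is 2(z₁₋α/₂ + z₀.₈)² / d², with d = 0.69:
- α = 0.05: 2(1.960 + 0.842)² / 0.476 = 33
- α = 0.025 per dose: 2(2.241 + 0.842)² / 0.476 = 40

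**The case against.** The strongest reply is that the 24-week question can be recovered from the article. The objective, all three hypotheses and the dropout rule point to 24 weeks, and the test description singles out total and delayed recall. A significant acute or post-treatment cell would answer none of the stated hypotheses. This stands: it would be wrong to say that any significant cell could pass as the primary result. But it shows that {12} conflicts with the other sections. It does not show that {12} is harmless.

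A reader might also infer that a false positive primary finding is more likely than not. The documents do not support that. It requires 56 separate unadjusted tests, any rejection in either direction counted as a primary finding, and a between-variable correlation no higher than about 0.9. {20a} plans a mixed model with a treatment-by-time interaction and does not prescribe 56 tests. Nor should the 50 versus 100 μg contrast be added to the count of chances for a false efficacy claim. The third hypothesis expects comparability, so a significant difference would count against it.

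Finally, {20a} does not say that 0.05 applies per comparison, and a multiplicity procedure may sit in an analysis plan that is not shown. That is fair for the procedure. It does not cover the choice of primary variable and time point, which belongs in the protocol and which this article answers in two ways.

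**Conclusion.** The point holds as an internal contradiction about the primary endpoint, together with unranked testing at a single stated level. The number of false-positive opportunities is not fixed by the article, so the honest statement of size is a range. It runs from about 9% on the narrowest reading, through 11–17% on the reading closest to the objective, to 44–84% on the broadest.

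All two-sided readings exceed 5%. This rests on no adjustment being applied, 24 analysed per arm, and assumed correlations. The contradiction itself rests on no assumption.

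**What to change.** In {12} and {20a}, before the interim unblinding:

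1. Name one 15-VLT variable as primary, either total immediate recall or delayed recall. The choice is the sponsor's. Define it as change from baseline to 24 weeks (T3), tested as the T3 treatment contrast from the mixed model.
2. Control the overall two-sided 0.05 over the two dose-versus-placebo comparisons, for example by Dunnett or Hochberg.
3. Make the other recall score at 24 weeks a key secondary, tested only after primary success.
4. Label the single-trial scores and the T1, T2 and T4 windows secondary or exploratory.

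The cost is wording, a registry update and some power. With a 0.025 split the two-group calculation goes from 33 to 40 per arm, and Dunnett or Hochberg costs no more than that split. Adjusting for the baseline score, which {20a} does not list among its covariates, may offset part of the loss. How much depends on a baseline-to-24-week correlation that the article does not give.
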